#### 1.4 Treatment groups

All subjects participating in the study (with or without anti-hypertensive/s) will be randomly assigned to either 'aggressive' or 'standard' BP target study arms. All subjects will have clinic BP maintained in the assigned target range over the duration of the study. Up or down titration of blood pressure during the trial will be performed as per the protocol. This will be monitored at least 4-monthly at the time of routine hospital visits. Patients already on anti-hypertensive medications at the time of study entry will continue on these or change as per clinical indication. ACEi or ARB's will be the mandatory first line agents. The dose of the agent will be adjusted to achieve the target blood-pressure levels with initial follow up at 2-4 weekly intervals following commencement of medication. The following order of escalation will be used (1) calcium channel blocker (CCB) (2) beta-receptor blocker (3) others such as diuretic or an alpha channel blockers. The preferential use of long acting drugs with once daily dosing would be recommended. This order of escalation will be used unless there are clear clinical indications for other agents. Amendments to the 'BP titration' procedures will be made if necessary following review of data after 20 subjects.

#### 1.5 Method of allocation of groups

After informed consent was obtained and eligibility confirmed, participants were randomised by the chief investigator using a rapid, secure, web-based randomisation system developed by the Kings Clinical Trial Unit, London. Randomisation to standard or intensive treatment arms (1:1) was stratified according to clinical centre.

In this open-label multi-centre trial participants and recruiting clinicians were informed of the participant's allocation and trial related systolic BP targets electronically. Therefore, no unblinding or code breaking is required. Further, those performing investigations were blind to participants SBP percentile and target, and the trial team and recruiters blinded to results.

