## EXPERIMENTAL DESIGN AND METHODS

### Protocol

**Subjects** (n=150, to give n=120 complete) will be aged 2 to 15 years with CKD stages 1-4 in the last 12 months. Subjects will be eligible to enter the study whilst on anti-hypertensive/s medications irrespective of recent change/s in anti-hypertensive therapy. Detailed inclusion and exclusion criteria are described later in this document under 'Section 3'. Subjects with arterio-venous fistulae, on dialysis or those with a previous kidney transplant at the time of study entry will be excluded. eGFR will be

calculated using the Schwartz formula and CKD staged as per existing definitions [31,32]. Patients who reach end stage renal failure and commence dialysis or receive a kidney transplant will stop participating in the 'randomised controlled trial' but continue to have measurements performed until the end of the study. Informed consent/assent will be obtained from parents and patients (if age applicable) for participation in the study, as per institutional ethics committee approval. A control group (n=120) of age matched children without CKD will be included with all proposed study related investigations to be performed at baseline and at annual intervals. These will be recruited from siblings of study subjects and from a local community using links from a school based liaison project. In addition we aim to recruit a further control group (n=30) of subjects with systolic BP <50th percentile but on no anti-hypertensive medication.

All study related investigations at 'baseline' will be performed just before randomisation. Following enrolment and performance of baseline investigations children with CKD will be randomised to the two arms of the study: aggressive BP control (below the 40th percentile) or standard BP control (between 50th-75th percentile). A minimisation procedure will be used to ensure that patients randomised to the two arms are matched for: age, gender, CKD stage and proteinuria. Children will be recruited over the first 12-months of the study and will therefore have at least 2-years of follow up. Following randomisation all children in whom blood pressure is not to target will be reviewed at 2-4 weekly intervals. Thereafter all children will be monitored at least 4-monthly at the time of routine hospital visits and have clinic BP maintained in the assigned target range over the duration of the study.

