## 2.4 Trial Statistics

*A description of the measures taken to avoid, or at least minimize, bias should be given. Specifically, this normally means describing the procedure(s) for randomisation and blinding. A description of the statistical methods to be employed, including timing of any planned interim analyses should also be provided. The number of subjects to be enrolled (in multicentre trials, the numbers of subjects for each site) should be stated, together with the rationale for the sample size (the "power calculation"). The level of significance that is to be used in each trial analysis must be stipulated, together with the procedure(s) for accounting for any missing, unused, and spurious data. Procedures for reporting any deviation from the original statistical plan should be described and justified. The data set for any analysis must be clearly stipulated (eg "all subjects", "randomised subjects", "intent to treat") and the population(s) should be clearly defined.*

Differences in outcome will be estimated using a random effects (mixed) model that includes the baseline value of the outcome. Sensitivity analyses will be performed to also include key prognostic variables including known factors other than blood pressure and those identified by univariate analyses.

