## **2.4.2 Randomisation**

Randomisation will be performed using the Institute of Psychiatry CTU online platform. Following consent baseline measurements will be performed immediately *before* randomisation. At external centres visiting investigators will perform measurements immediately before randomisation.

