### **3.1 Main analysis of treatment differences**

Mixed effects models will be used to estimate the mean annual rate of change and the difference in these rates between treatment arms. Models will account for baseline and all subsequent follow-up time points.

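### Protocol and SAP describe different allocation schemes, and the primary mixed model includes no allocation factor under either, so its interval may be too wide

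*Combined protocol and SAP*

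**What the plan says.** **Allocation.** The Protocol subsection of Experimental Design and Methods states: "A minimisation procedure will be used to ensure that patients randomised to the two arms are matched for: age, gender, CKD stage and proteinuria". Centre is not mentioned. Protocol 2.4.2, where a reader would look for the scheme, gives only the system: "Randomisation will be performed using the Institute of Psychiatry CTU online platform". SAP 1.5, written in the past tense, reports: "Randomisation to standard or intensive treatment arms (1:1) was stratified according to clinical centre". It mentions neither minimisation nor any of the four patient factors.

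**Primary model.** Protocol 2.4 states: "Differences in outcome will be estimated using a random effects (mixed) model that includes the baseline value of the outcome". SAP 1.9 also adjusts for the baseline outcome. SAP 3.1 defines the target: "Mixed effects models will be used to estimate the mean annual rate of change and the difference in these rates between treatment arms". It adds: "Models will account for baseline and all subsequent follow-up time points". None of these sections names centre, age, sex, CKD stage or proteinuria.

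**Adjusted analysis.** Protocol 2.4 has one: "Sensitivity analyses will be performed to also include key prognostic variables including known factors other than blood pressure and those identified by univariate analyses". The variables are not listed and the analysis is not tied to the allocation factors. The SAP does not carry it over. Its only sensitivity analysis (3.1.4) relaxes linearity over time.

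**The concern.** A reader cannot tell how the children were allocated, and therefore cannot tell which factors the analysis should reflect. That has to be settled whatever the numerical effect.

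The second issue is statistical. Balancing the arms on a factor that predicts the outcome removes that factor's contribution to chance differences between arms. A model without the factor still counts that contribution as noise, so its standard error is larger than the true sampling variability. What is at stake is some precision and power in the primary comparison.

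The only covariate-adjusted analysis in either document has an open variable list, part of which would be chosen by looking at the trial data.

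**Working it through.** **1. The plan's own power figure.** Inputs from protocol 2.4.1 and SAP 1.8: 60 per arm, difference 3.1 g/m^2.7, SD of change 6, P<0.05. I take the test as two-sided because a 95% CI is planned.

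- SE = 6 × √(2/60) = 1.095.
- Power = Φ(3.1/1.095 − 1.96) = Φ(0.87) = 80.8%.

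The stated 90% does not reproduce. It would need (1.96 + 1.2816)² × 2 × 36/3.1² = 78.7, or 79 per arm. One-sided 0.05 gives 88.2%, but no one-sided test is stated. This is a separate matter; 80.8% is the starting point used here.

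**2. Effect of omitting factors used to balance.** Let R² be the share of variance in LVMI change that the allocation factors explain. The documents give no value, so a range is assumed. With close balance, the true SE of the unadjusted estimate is √(1−R²) times the SE its model reports. With SE = 1.095:

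- Coverage = 2Φ(1.96/√(1−R²)) − 1
- Unadjusted power = Φ((3.1 − 1.96 × SE)/(SE × √(1−R²)))
- Adjusted power = Φ(3.1/(SE × √(1−R²)) − 1.96)

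| Assumed R² | Interval too wide by | Coverage | Type I error | Power, unadjusted | Power, adjusted | Points lost |
|---|---|---|---|---|---|---|
| 0 | 0% | 95.0% | 5.0% | 80.8% | 80.8% | 0 |
| 0.1 | 5.4% | 96.1% | 3.9% | 82.0% | 84.7% | 2.7 |
| 0.2 | 11.8% | 97.2% | 2.8% | 83.5% | 88.6% | 5.1 |
| 0.3 | 19.5% | 98.1% | 1.9% | 85.1% | 92.3% | 7.2 |

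**3. Simulation.** 3,000 trials per scenario, ordinary regression on change. One set used permuted blocks of 4 within the 14 centre sizes of Table S4 (1 to 47 children, total 124). The other used minimisation on four factors with probability 0.8. Block size and probability are assumptions.

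- R² 0.1: unadjusted coverage 95.5% (centre) and 95.9% (minimisation).
- R² 0.3: unadjusted coverage 97.1% and 97.0%. This is below the formula's 98.1%, as expected when balance is imperfect.
- Adjusted coverage was 94.3 to 95.3% throughout.

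**4. What adjustment must look like for a slope.** SAP 3.1 compares annual rates of change, so a factor that shifts only the level of LVMI matters little. In a random-intercept model with visits at years 0, 1 and 2, I used SD of level 9.1 (the sponsor's cohort, protocol Background) and SD of change 6. This gives a within-child correlation of 1 − 36/(2 × 82.81) = 0.783. Over 600 trials, a factor explaining 30% of level variance moved the model SE of the slope difference only from 0.516 to 0.501 when added, and unadjusted coverage was about 95%.

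For a factor explaining 20% of the variance in change, a small run (25 trials, random intercept and slope) gave median SEs of 0.536 unadjusted, 0.529 with a main effect and 0.472 with a factor-by-time term. The last ratio, 0.472/0.536 = 0.88, is close to the expected √0.8 = 0.89. The gain comes from the interaction with time.

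**The case against.** The strongest reply is that the model already uses baseline LVMI and estimates a slope, and nothing in the documents shows that the allocation factors predict *change*. A reader might infer that age must be prognostic because LVH is defined by age-specific limits. Those limits show that age relates to the level of LVMI, not to its change. The evidence on LVH itself is mixed: the protocol Background cites one study with associations for male gender and reduced GFR, and reports no association with male gender in the sponsor's own cohort. This stands. The loss could be nil, and it is under 3 points at R² of 0.1 or less.

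A reader might also set the adjusted powers of 84.7, 88.6 and 92.3% against 80.8% and infer gains of 3.9, 7.8 and 11.5 points. That comparison fits only factors *not* used in allocation, for which the unadjusted interval is not too wide. Both consequences cannot be claimed for the same factor. By the same reasoning, it does not follow that all five factors belong in the model as allocation factors. Under the SAP's scheme that is centre alone; under the protocol's it is the four patient factors.

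Finally, protocol 2.4 does plan an adjusted sensitivity analysis. That is a partial answer only, because its list is open, partly data-selected, and absent from the SAP.

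**Conclusion.** The point holds in two parts. The contradiction over allocation is a matter of record and rests on no assumption. So does the absence of every candidate allocation factor from the primary model.

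The consequence is conditional. If the factors actually balanced predict LVMI change, the unadjusted interval is too wide: coverage is about 95 to 98% and the power lost about 0 to 7 points for assumed R² of 0 to 0.3. These figures rest on 60 per arm, SD 6, difference 3.1, a two-sided 5% test and close balance.

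A reader might infer that the trial's intervals are invalid or that false positives are inflated. Neither follows: type I error falls below 5%. Nor would dropping minimisation in favour of centre stratification bias the comparison, since allocation is still random. It would only leave balance on the four patient factors to chance. The change is worth making because it is nearly free, not because the primary result would otherwise be unsafe.

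**What to change.** 1. Confirm from the randomisation system which scheme and which factors were used. State them identically in the protocol's Experimental Design and Methods, protocol 2.4.2 and SAP 1.5.
2. In SAP 3.1, pre-specify those factors in the primary model, each with a factor-by-time term because the estimand is a difference in annual slopes. Main effects alone would recover little.
3. If centre was a factor, fit it as a random effect: an intercept and, if estimable, a slope. Table S4 has one centre with 1 child, four with 3 or 4, and one with 47, so fixed centre effects are impractical.
4. Any of age, sex, CKD stage and proteinuria not used in allocation may be added as pre-specified precision covariates.
5. Replace the open selection rule in protocol 2.4 ("including known factors other than blood pressure and those identified by univariate analyses") with this named list, and report the unadjusted model as a sensitivity analysis in SAP 3.1.4.

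Cost: wording, plus a few degrees of freedom in about 120 children. Demographics, blood and urine samples are already scheduled at day 1, so no new data are needed.

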#### 1.6 Frequency and duration of follow-up

Participants will complete follow up measures as describe in Table 1

**Table 1. Trial Completion dates**

| Key task completion date (months)            | Day 1                                 | 4-mths | 8-mth | 1 year | 2 year | 3 year |
|----------------------------------------------|---------------------------------------|--------|-------|--------|--------|--------|
| Patient information and informed consent     | Over first 12 months of study         |        |       |        |        |        |
| Physical examination                         | At recruitment and at least 4 monthly |        |       |        |        |        |
| Demographics                                 | √                                     | √      | √     | √      | √      | √      |
| Clinic BP and review of medications          | √                                     |        |       | √      | √      | √      |
| ABPM (in sub-group)                          | √                                     |        |       | √      | √      | √      |
| Central BP evaluation                        | √                                     |        |       | √      | √      | √      |
| Blood sample                                 | √                                     |        |       | √      | √      | √      |
| Urine sample                                 | √                                     |        |       | √      | √      | √      |
| Non-invasive arterial studies (cIMT and PWV) | √                                     |        |       | √      | √      | √      |
| Echocardiography                             | √                                     |        |       | √      | √      | √      |
| 24-hour ambulatory BP monitoring             | √                                     |        |       | √      | √      | √      |

### **1.7 Data collection/Trial Procedure**

Clinic BP measurements performed over a 3-month period immediately prior to entry to study will be used to calculate average Clinic BP percentile.

On entry into the study a detailed history will be taken and case records reviewed to determine the cause and duration of CKD, past and family history relevant to CKD/CVD. Ethnicity (self defined by parents) will be recorded. The following measurements/records will be obtained on the first and subsequent visits:

- a. The clinical history will be updated together with details of current medications including hypertensive treatment, phosphate binders and hydroxylated vitamin D. A clinical examination will be performed. Height (stadiometre), weight, body mass index (BMI) and waist circumference will be recorded. Urine and blood biochemistry will be performed on the first and at annual visits.
- b. Urine samples will be collected at study entry and at annual review. First morning voids on the three days prior to clinic visit will be required. The patient will keep urine specimens in a home refrigerator at 4 °C before clinic visits. Specimens will be centrifuged to separate the cellular component from the supernatant and stored at -80 °C. A mean value of three Ualb/Ucreat will be recorded.
- c. In addition to serum urea, electrolytes creatinine and cystatin C, the following biomarkers related to arterial injury, calcification and ventricular load will be determined:
  - i. Arterial injury: lipid profiles (total cholesterol, LDL-cholesterol, HDL-cholesterol, triglycerides and Apolipoprotein-B), homocysteine, high sensitivity CRP.
  - ii. Arterial calcification: plasma calcium, plasma phosphate and calcium-phosphate product ( $\text{Ca} \times \text{PO}_4$ ), plasma intact parathyroid hormone (iPTH), FGF23, 25(OH) vit D, 1,25 (OH) vit D, blood haemoglobin (Hb).
  - iii. Ventricular load: N-terminal pro-B type natriuretic peptide (NT-proBNP).
- d. Clinic blood pressure
  - i. Clinic blood pressure will be taken as the mean of 3 measurements using the appropriate sized cuff and a calibrated aneroid instrument according to current guidelines. All observers will undergo appropriate training including the evaluation of their variation from independent experienced investigators. Normative criteria will be those defined in the Fourth report of the National High Blood Pressure Education Program Working Group in the United States ('Fourth report') and will be expressed as z-scores.
- e. 2D-guided M-mode echocardiography will be performed using images obtained in either parasternal long axis or short axis view of the left ventricle, as recommended by the American Society of Echocardiography. ECHO studies will be performed by trained paediatric echocardiographers using a Philips iE33 ultrasound system (Philips Inc, Andover, Mass, USA). All studies will be stored digitally and analysed by a single investigator ([name]) who will be blinded to the medical history. Left ventricular mass will

be calculated using the Devereux equation. Left ventricular mass varies widely across the paediatric age range, therefore to allow standardisation it is usually expressed as left ventricular mass index (LVMI). We will use LVMI (LVM divided by height in meters raised to allometric power of 2.7 [ $\text{g}/\text{m}^{2.7}$ ]) as a measure of LVH that accounts for body size. LVH will be defined as  $\text{LVMI} \geq 95\text{th percentile}$  using age-specific reference intervals for normal children, where appropriate, we will also calculate left ventricular mass for height z-scores. Relative wall thickness (RWT) will be measured to assess the left ventricular geometry. Patients with increased LVMI ( $\geq 95\text{th percentile}$ ) and elevated RWT ( $\geq 0.41$ ), have concentric LVH; with increased LVMI ( $\geq 95\text{th percentile}$ ) and normal RWT ( $< 0.41$ ) have eccentric LVH; and those with normal LVMI ( $< 95\text{th percentile}$ ) and elevated RWT ( $\geq 0.41$ ) have concentric remodelling. Shortening fraction will be calculated to estimate the LV systolic function. Diastolic function will be assessed by pulsed Doppler interrogation of mitral valve inflow and tissue velocity imaging interrogation at the level of the mitral valve annulus both at the septum and left ventricular free wall. The mitral valve E/e' ratio will be used as a surrogate for filling pressures. Cross sectional images in both four chambers and multiple short axis views will be obtained to permit analysis of myocardial rotation and torsion using two dimensional strain ("speckle tracking") techniques.

### **1.8 Sample size estimation (including clinical significance)**

The original sample size calculations were based upon longitudinal measurements of LVMI at annual intervals in our cohort of children with CKD ( $n=47$ ). The SD of change in LVMI is  $7.7 \text{ g}/\text{m}^{2.7}$  and this was obtained without the same standardized reading of LVM that we are proposed in the study. To be conservative we assume just a 20% improvement on our existing data giving an SD of  $6 \text{ g}/\text{m}^{2.7}$  result from our own cohort. Thus with  $n=60$  in each group we should be able to detect a difference in change in LVMI of  $> 3.1 \text{ g}/\text{m}^{2.7}$  ( $=9\%$  of baseline LVMI) over the 2 year duration with 90% power ( $P<0.05$ ). This is one third of the difference ( $9.4 \text{ g}/\text{m}^{2.7}$ ) between subjects in our cohort that have blood pressure in the 50-75th and below 40th percentiles. Although we are assuming relatively rapid tracking of LV mass in relation to blood pressure, this is not unreasonable given the time frame of LV regression in adults. A recent meta-analysis [Fagard et al, Hypertension 2009; 54:1084] of randomized studies shows a mean change in LVMI of 10.3% over duration of 6 months.

### **1.9 Brief description of proposed analyses and any pre-analysis statistical checks required**

The outcome data are longitudinal and so we will fit a model that takes account of this data structure. The random effects model is a 2-level multilevel model that allows for the repeated data within subjects, while allowing some measurements to be missing. (This is preferred to repeated measures analysis of variance that requires complete data on all subjects). For a particular outcome, eg LVmass, the baseline value for each subject will be included in the model to adjust for (random) baseline variability between subjects. The results of the analysis are in the form of mean difference in LVmass between the intervention and control groups, at the endpoint, with a 95% CI.

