### 2.4.1 Sample Size

The outcome data are longitudinal and so we will fit a model that takes account of this data structure. The random effects model is a 2-level multilevel model that allows for the repeated data within subjects, while allowing some measurements to be missing. (This is preferred to repeated measures analysis of variance that requires complete data on all subjects). For a particular outcome, eg LVmass, the baseline value for each subject will be included in the model to adjust for (random) baseline variability between subjects. The results of the analysis are in the form of mean difference in LVmass between the intervention and control groups, at the endpoint, with a 95% CI.

The original sample size calculations were based upon longitudinal measurements of LVMI at annual intervals in our cohort of children with CKD (n=47). The SD of change in LVMI is 7.7 g/m2.7 and this was obtained without the same standardized reading of LVM that we are proposed in the study. To be conservative we assume just a 20% improvement on our existing data giving an SD of 6 g/m2.7 result from our own cohort. Thus with n=60 in each group we should be able to

detect a difference in change in LVMI of  $> 3.1 \text{ g/m}^{2.7}$  (=9% of baseline LVMI) over the 2 year duration with 90% power ( $P<0.05$ ). This is one third of the difference ( $9.4 \text{ g/m}^{2.7}$ ) between subjects in our cohort that have blood pressure in the 50-75th and below 40th percentiles. Although we are assuming relatively rapid tracking of LV mass in relation to blood pressure, this is not unreasonable given the time frame of LV regression in adults. A recent meta-analysis [Fagard et al, *Hypertension* 2009; 54:1084] of randomized studies shows a mean change in LVMI of 10.3% over duration of 6 months.

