## **2. Data analysis plan – Data description**

### **2.1 Baseline comparability of randomised groups**

Baseline descriptions of participants by treatment and overall will be reported using means and standard deviation or numbers and proportions as appropriate. No significance testing will be used.

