#### **3.1.1 Model assumptions**

Mixed effect models will assume a linear change in outcome over time.

It will be assumed that there is no difference between treatment arms at baseline (as confirmed by baseline comparability (Section 2.1).

Missing data from loss to follow-up/withdrawal will be assumed missing at random.

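### SAP 1.9 and 3.1 give baseline LVMI two roles and never name a random slope; applied together with a random intercept only, they would raise the type I error to about 13–15%

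*Combined protocol and SAP*

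**What the plan says.** SAP 1.9 (carried over from protocol 2.4.1) describes a 2-level random effects model for repeated data within children. On baseline it states that "the baseline value for each subject will be included in the model to adjust for (random) baseline variability between subjects". On output it promises an endpoint comparison, reported with its confidence interval (95% level): "The results of the analysis are in the form of mean difference in LVmass between the intervention and control groups, at the endpoint, with a".

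SAP 3.1 sets a different target, the difference between arms in mean annual rate of change, and adds: "Models will account for baseline and all subsequent follow-up time points".

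SAP 3.1.1 assumes linear change over time and then: "It will be assumed that there is no difference between treatment arms at baseline (as confirmed by baseline comparability (Section 2.1"). SAP 2.1, cited there as confirmation, is a descriptive table for which "No significance testing will be used".

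No section lists the response vector, the fixed effects or the random effects. The only planned sensitivity analysis (3.1.4) relaxes linearity.

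**The concern.** Baseline can enter a longitudinal model as a covariate, with follow-up visits as the responses, or as the time-0 response. Section 1.9 reads as the first. Sections 3.1 and 3.1.1 read more like the second, with the arm main effect left out because the arms are taken as equal at time 0. Nothing says that these are separate models.

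If both roles are used, the time-0 response is almost fully explained by its own covariate, while follow-up visits still vary between children. A single random intercept has to average over both, so it understates the between-child variance after baseline. With no arm term, that unmodelled variance falls on the arm-by-time coefficient, which is the primary comparison.

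The random slope is a second matter. If children truly differ in rate of change, a random-intercept model omits the variance that governs a comparison of rates. At stake are the width of the primary interval and the size of the primary P value.

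**Working it through.** **Inputs**
- 60 per arm and SD of change 6 g/m^2.7, from the sample size sections (protocol 2.4.1, SAP 1.8).
- Annual echocardiography at years 0–3, from SAP Table 1. Years 0–2 and the attendance pattern of Figure S6 (years 0–5) were also run.
- Baseline SD of LVMI: 10.1 and 8.1 in Table S2, and 9.1 in the protocol background.
- Between-child slope SD *s*: not in the documents. Assumed range 0 to 3 g/m^2.7 per year.

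**The plan's own figure.** The documents give no type I error for the mixed model. The sample size calculation supplies the SD: SE = 6√(2/60) = 1.095; 3.1/1.095 = 2.83; two-sided power = Φ(2.83 − 1.96) = 0.81, against the stated 90%. That mismatch is a separate issue and does not affect this point.

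**Variances.** With equal slopes, residual variance = 6²/2 = 18. Between-child SD 8 gives total variance 64 + 18 = 82 (SD 9.06). For *s* > 0 the residual variance is 18 − 2*s*², so the SD of 2-year change stays at 6. At *s* = 3 this reaches 0 (a residual SD of 0.5 was used), so 3 is an extreme.

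**Double use by hand (years 0–3, equal slopes, random intercept, no arm term)**
1. Visit correlation: 64/82 = 0.780. Given baseline, follow-up visits share variance 64 × 18/82 = 14.05, and time 0 has none.
2. One coefficient on baseline must serve all four visits: (1 + 3 × 0.780)/4 = 0.835. The leftover loading is 1 − 0.835 = 0.165 at time 0 and 0.780 − 0.835 = −0.055 afterwards.
3. Covariance is 14.05 + 0.055² × 82 = 14.30 for each of the three follow-up pairs, and −0.165 × 0.055 × 82 = −0.74 for each of the three pairs with time 0. The fitted intercept variance is their average: (3 × 14.30 − 3 × 0.74)/6 = 6.78, about half of 14.05.
4. Model SE: θ = 6.78/(18 + 4 × 6.78) = 0.150. Information per child = (14 − 36θ)/18 = 0.477. SE = 1/√(30 × 0.477) = 0.264, where 30 = 120/4.
5. True SE: the visit weights (t − 6θ)/18 are −0.050, 0.005, 0.061 and 0.117, and the last three sum to 0.183. Variance per child = 14.05 × 0.183² + 18 × (0.005² + 0.061² + 0.117²) + 82 × (0.165 × 0.050 + 0.055 × 0.183)² ≈ 0.81. SE = √(0.81/(30 × 0.477²)) ≈ 0.344.
6. Rejection rate = 2{1 − Φ(1.96 × 0.264/0.344)} ≈ 13%.

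Repeated simulation of the same case gave 13.1% to 14.9%, with model SE 0.264 and empirical SE 0.346 to 0.352.

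**Simulated type I error (%), nominal 5%, random intercept only**

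| Role of baseline | Visits | s=0 | s=1 | s=2 | s=3 |
|---|---|---|---|---|---|
| Covariate and response, no arm term | years 0–3 | 13.6 | 18 | 24 | 31 |
| same | years 0–2 | 14.4 | 15.1 | 19.1 | 26.7 |
| same | Figure S6 pattern | 13.3 | 24 | 36 | 46 |
| Covariate and response, with arm term | years 0–3 | 5.2 | 9 | 15 | 25 |
| Response only | years 0–3 | 5.1 | 8 | 17 | 27 |
| same | years 0–2 | 4.9 | 4.8 | 10.0 | 18.7 |
| same | Figure S6 pattern | 4.1 | 13.7 | 28.3 | 41.6 |

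Each entry rests on at least 1,000 trials (Monte Carlo SE at 14%: √(0.14 × 0.86/1000) = 1.1 points).

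**With a random slope added**, pooled over 21 settings (3,150 trials; Monte Carlo SE √(0.05 × 0.95/3150) = 0.4 points): response only 5.4%, double use 5.3%.

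**The case against.** The strongest reply is that the SAP does not contain the failing model. A 2-level model means visits within children and can carry a random slope. With one, the error is near 5% even when baseline is used twice. Sections 1.9 and 3.1 have different estimands, so they may describe two models, and the phrase about accounting for baseline is loose. Taken alone, section 3 already points to baseline as a response with a common mean. The double-use inflation needs three choices together: both roles for baseline, no arm term and no random slope. The first two are only suggested by the text. All of this stands, and it makes the inflation conditional.

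What remains is that the sections conflict on estimand and on the role of baseline. Following them literally with the simplest 2-level model gives a wrong standard error, and the linearity sensitivity analysis is not designed to reveal it.

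Three stronger inferences are not supported:
- **That the primary P value is over-precise as a matter of fact.** The documents do not say which random effects were or would be fitted.
- **That the baseline LVMI gap in Table S2 (31.9 against 30.3) demonstrates the problem.** Its SE is √(10.1²/64 + 8.1²/60) = 1.64, so the gap of 1.6 is under one SE. It says nothing about over-precision, and it is not comparable with a target difference in change.
- **That the model is chosen on observed balance.** Section 3.1.1 states an assumption and names no alternative model if the arms differ. The wording about confirmation is wrong as a justification but has no operational effect.

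**Conclusion.** The point holds in conditional form. The SAP leaves the role of baseline and the random effects open, and gives two estimands for the primary outcome. The permitted readings run from a valid analysis at about 5% to one at about 13–15% with equal true slopes, and higher if slopes vary.

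The 13–15% figure assumes double use of baseline, no arm main effect and a random intercept only. It changes little with the visit schedule when true slopes are equal. It largely disappears with an arm main effect if true slopes are equal, or with a random slope in any case.

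The separate cost of omitting a random slope, with baseline as a response only, is about 8% and 17% at slope SDs of 1 and 2 per year for visits at years 0–3. It is smaller over two years (4.8% and 10.0%) and larger with longer follow-up. Those slope SDs are assumptions.

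**What to change.** State one primary estimand and one model, in the same words in 1.9 and 3.1. For the slope comparison:

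LVMI at visit *j* of child *i* = β₀ + β₁·time + β₂·(arm × time) + b₀ᵢ + b₁ᵢ·time + error

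- Baseline LVMI is the time-0 response with a common mean across arms. It is not also a covariate.
- Each child has a random intercept and a random slope. If visit is treated as categorical, use an unstructured covariance instead.
- β₂ is the primary comparison. If a difference at a stated visit is wanted as well, define it from the same model.
- In 3.1.1, justify the common baseline mean by randomisation and delete the claim that the descriptive table confirms it.

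The cost is SAP wording and one extra variance term. The downside is wider intervals wherever children differ in rate of change; those intervals reflect the real uncertainty.
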